### Assessment of joint pain and knee function

Subjects will be provided an assessment of their joint pain level using the 100 mm visual analog scale (VAS) at 6-week intervals.

Knee Injury and Osteoarthritis Outcome Score (KOOS) questionnaire will be used to measure a subject's opinion about their knee and associated problems [21]. The KOOS consists of 42 questions, which cover five domains. These include (1) pain frequency and severity during functional activities; (2) severity of knee stiffness and swelling, grinding or clicking, catching, and limitation in range of motion; (3) difficulty in performing the daily living activities; (4) difficulty experienced during sport and recreational activities; and (5) knee-related quality of life (QOL).

All items are scored on a 5-point Likert scale (0–4). The five dimensions are scored separately as the sum of all corresponding items. Scores are then converted to a 0–100 scale (percentage of total possible score obtained), where zero represents extreme knee problems and 100 represents no knee problems.

### Statistical analysis

Statistical analysis will be performed using IBM statistics software version 25 (Armonk, NY, USA). The values of variables will be presented as mean ± standard deviation. Normality tests will be assessed through Shapiro-Wilk tests carried out on each parameter before analysis. Analysis includes all the participants (intent to treat) determining the baseline characteristic. Additional analysis will be performed per protocol on participants with 80% or higher adherence to study protocol. Two-way repeated measures ANOVA will be used to determine differences within groups (pre vs. post) as a repeated factor and intervention (GSM vs. placebo) as a fixed factor, with the model adjusted for the BMI and age, physical activity, and baseline vitamin D status. Post hoc analysis with Bonferroni adjustments will be performed for multiple comparisons. Statistical significance will be set at a level of 0.05.

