### Sample size

The sample size calculation applies to CTX-II/creatinine, CTX-II/procollagen II C-propeptide (PIICP) also referred as (CPII) CPII ratio, and cartilage oligomeric matrix protein (COMP) as the primary outcome variables. For CTX-II/ creatinine as well as CTX-II/ CPII a sample size of 24 is required to detect a 20% relative difference from baseline with 80% power. Hence, 25 subjects will be recruited for each group (GSM and placebo). For COMP as well as CPII a sample size of 7 is required to detect a 20% difference from baseline. This randomized double-blind placebo-controlled trial in parallel design recruit 55 (allowing for 10% potential dropout rate, with 27–28 sample in each arm).

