### Study outcomes

#### Primary outcomes

The difference in the mean of cartilage turnover markers (CPII, COMP, CTX-II) and bone resorption marker (CTX-I), measured at the end of the study in comparison with the week 6 and baseline values.

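### The primary outcome, sample size and ANOVA are worded as change from baseline within groups; no between-arm test is named as decisive, and week 6 has no place in the pre/post factor

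*Protocol article*

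**What the plan says.** Three sections of the protocol article bear on the primary comparison.

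- **Primary outcomes** takes the mean cartilage and bone markers "measured at the end of the study in comparison with the week 6 and baseline values". No comparator arm is mentioned.
- **Sample size** states, for CTX-II/creatinine and CTX-II/CPII, that "a sample size of 24 is required to detect a 20% relative difference from baseline with 80% power". For COMP and CPII, "a sample size of 7 is required to detect a 20% difference from baseline". No SD is given, and the article does not say whether these are paired or two-group calculations.
- **Statistical analysis** states: "Two-way repeated measures ANOVA will be used to determine differences within groups (pre vs. post) as a repeated factor". The sentence goes on "and intervention (GSM vs. placebo) as a fixed factor", "with the model adjusted for the BMI and age, physical activity, and baseline vitamin D status". The marker's own baseline value is not among the covariates. No interaction and no week-12 contrast is named.

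The Procedure section and Table 1 schedule blood and urine at baseline, week 6 and week 12.

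**The concern.** In a placebo-controlled trial the evidence for the product is the difference between the randomised arms. Here the outcome, the size calculation and the stated aim of the ANOVA all point to change over time instead. An analyst who follows the text could report a significant fall in the GSM arm beside a non-significant one in the placebo arm and call that efficacy. Another could read the ANOVA's group main effect, which averages pre and post values and so dilutes the treatment effect. A third could read group-by-time, which is a proper between-arm test. The article does not say which of these decides.

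There is also a direct conflict over time points. The primary outcome names week 6, but a pre/post factor has two levels, so the model as worded cannot deliver the stated outcome.

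The Discussion looks ahead to wide use of GSM powder if it reduces cartilage degradation. Only a between-arm result can support that.

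**Working it through.** **The plan's own figure.** The 24 can be neither reproduced nor refuted, because no SD is given. The SD that yields it can be back-solved for a 20% difference, 80% power and two-sided 0.05 (sidedness assumed), with 1.96 + 0.84 = 2.80:

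- Paired test within one group: SD of change = 20 × √24 / 2.80 = 35.0%.
- Two-sample test, 24 per arm: SD = 20 × √(24/2) / 2.80 = 24.7%.

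With 25 per arm, normal-approximation power for a 20% between-arm difference is Φ(20 / (SD × √(2/25)) − 1.96). This gives 52% at SD 35.0% and 82% at SD 24.7%. What the 24 refers to therefore matters, and the words used do not settle it.

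**If within-arm tests decided.** Suppose there is no treatment effect, both arms change equally, and each within-arm test is significant with probability p. The arms are independent, so P(GSM significant, placebo not) = p(1 − p).

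- p = 0.8: 0.8 × 0.2 = 0.16.
- Maximum, at p = 0.5: 0.25.
- Paired t-test, 25 per arm, SD of change 35%: a shared change of 10%, 14% or 20% gives p = 0.28, 0.48 or 0.78, and p(1 − p) = 0.20, 0.25 or 0.17.

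The range is thus about 16% to 25%. In the paired t-test cases GSM alone is significant against its own baseline 28% to 78% of the time with no treatment effect.

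**Which ANOVA term is read.** Take a treatment effect δ at post only, equal SD at both times, and correlation ρ between them. The standardised effects, in units of δ/SD, at an assumed ρ = 0.7 are:

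- Group main effect: 0.5 / √((1 + ρ)/2) = 0.5 / √0.85 = 0.54.
- Group-by-time (the change contrast): 1 / √(2(1 − ρ)) = 1 / √0.60 = 1.29.
- ANCOVA on baseline: 1 / √(1 − ρ²) = 1 / √0.51 = 1.40.

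Power for a 20% effect with 25 per arm and SD 24.7% is Φ(d / √(2v/25) − 1.96). Here d = 10 and v = SD²(1 + ρ)/2 for the main effect; d = 20 and v = 2·SD²(1 − ρ) for group-by-time; d = 20 and v = SD²(1 − ρ²) for ANCOVA.

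| ρ (assumed) | Main effect | Group-by-time | ANCOVA |
|---|---|---|---|
| 0.3 | 43% | 68% | 85% |
| 0.5 | 38% | 82% | 91% |
| 0.7 | 34% | 96% | 98% |
| 0.9 | 31% | >99% | >99% |

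At a marker SD of 35% the ranges over the same correlations are 18–24%, 40% to over 99%, and 56% to over 99%.

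**Gain from using baseline as a covariate.** The variance ratio of ANCOVA to change score is (1 − ρ²) / (2(1 − ρ)) = (1 + ρ)/2. It is 0.75 at ρ = 0.5, 0.85 at 0.7 and 0.90 at 0.8, a reduction of 25%, 15% and 10%.

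**The case against.** The strongest reply is that the randomised comparison is already in the model. The sentence on the ANOVA enters intervention as a fixed factor, and a two-way analysis with time within subjects and arm between subjects ordinarily produces the group-by-time test. With two time levels that test is the between-arm difference in change. This stands. A reader might infer that the trial has no between-arm test at all, and the text does not support that.

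Second, this is a condensed article, and naming the deciding contrast is often left to an analysis plan, which may exist and is not shown. Silence alone would be no finding. But the article is not merely silent: it states an outcome, a size target and an analysis aim that all refer to change from baseline, and an analysis plan would have to override them.

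Third, the 16–25% and 0.54 figures apply only if within-arm tests or the group main effect decide, and the article announces neither. They measure what the ambiguity allows, not the error rate of a declared test.

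Fourth, restricted foods and supplements stop four weeks before the trial begins, and baseline samples follow that washout. Much of any change from stopping may therefore precede baseline. This weakens the case for a shared change but does not remove it, since the food restriction runs to week 12 in both arms.

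Fifth, leaving out the marker's baseline value might be read as a failure to account for baseline. It is not: baseline is a level of the repeated factor, so group-by-time uses it.

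**Conclusion.** The point holds in a limited form. The primary outcome, the sample-size target and the stated aim of the ANOVA are all worded as change from baseline, while the available between-arm test is not named as decisive. The conflict over week 6 is plain, but it lies only between the ANOVA wording and the primary outcome; the outcome itself includes week 6.

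The consequence ranges from small to serious. If group-by-time is what the investigators intend, inference is valid and the loss is one of efficiency: 1.29 against 1.40 at ρ = 0.7, or 10% to 25% of variance for ρ from 0.8 to 0.5. If within-arm tests were used, a shared change could produce a spurious GSM-only result in about 16% to 25% of trials. If the main effect were read, power for a 20% effect would be 31% to 43% at SD 24.7%.

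The SDs are back-solved and the correlations assumed; the article gives neither. The 52% power under the paired reading might be taken as proof that the trial is too small. It is not, because the two-sample reading gives 82% and the article does not say which applies.

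**What to change.** Define the primary estimate as the GSM-minus-placebo difference at week 12, with a 95% CI. Take it from a repeated-measures model with weeks 6 and 12 as outcomes and with arm, visit and arm-by-visit terms. Enter the marker's own baseline value as a covariate, and not also as an outcome level. Keep the covariates already planned: BMI, age, physical activity and baseline vitamin D.

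Reword Sample size, Primary outcomes and Statistical analysis to match. In Sample size, give the SD used and say whether 24 is per arm for a between-arm comparison. Label within-arm changes, including week 12 against week 6, as descriptive.

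The cost is wording and a changed model specification. All the data are already scheduled for collection. The Trial status section shows data collection still under way at this version, and the Intervention section places unblinding at the end of the study, so the change can be made without knowledge of the results.

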## Discussion

To the best of our knowledge, this is the first randomized controlled trial that will determine the effect of whole meat GSM powder on cartilage metabolism, bone resorption, and inflammation biomarkers in overweight and obese postmenopausal women who at high risk of developing OA. The current study builds on a promising pre-clinical trial [14] which confirmed the chondroprotective effect of GSM powder in an experimental model of metabolic OA by reducing the CTX-II (decreasing type II collagen degradation) without any apparent adverse effects.

The current study aims to address several gaps in the current scientific evidence for GSM interventions. Firstly, until now there have been a limited number of studies which investigated the effectiveness of whole GSM extract interventions on clinical symptoms of OA in individuals with diseased state [13, 22]. The current study will include biomarkers of cartilage turnover and inflammation to address the paucity of evidence on cartilage-protective effectiveness of GSM intervention in healthy individuals without OA. Secondly, this trial aims to target overweight and obese postmenopausal women, a population group more severely impacted by OA [23], and given the limited number of interventions in this population, this study will address this specific gap in the current evidence base.

The current study has limitations. Firstly, participants are postmenopausal women, therefore findings cannot be extrapolated to a male population. Secondly, this study aims to investigate the preventive effects of GSM against early-stage OA associated with obesity and metabolic syndrome at healthy individuals. Given the fact that stage and phenotype of OA with distinct etiology could have an impact in terms of treatment response, therefore patients with age or trauma-induced or advanced OA may not benefit from the result of this study [24].

To conclude, if the whole meat GSM intervention reduces the cartilage degradation and improves the cartilage synthesis, there is potential for the wide implementation of GSM powders as dietary supplements or functional foods, or even as a whole food to prevent or delay the onset of OA.

## Trial status

Recruitment began on 1 July 2020. Currently, recruitment is completed, and data collection is expected to be completed in September 2021. The current protocol version is 3.0, dated 27 May 2021.

## Data Availability

The data that support the findings of this study are available from the corresponding author, [name] upon reasonable request.
